## Abstract

**Background:**

Asthma causes substantial morbidity and mortality in the United States, particularly among African American emerging adults (AAEAs; aged 18-30 years), but very few asthma programs have targeted this population. Interventions that provide education and address underlying motivation for managing asthma may be the most effective. However, intensive face-to-face interventions are often difficult to implement in this population.

**Objective:**

The purpose of this study is to develop an effective mobile asthma management intervention to improve control among AAEAs.

**Methods:**

We will assess the ability of multiple technologic components to assist and improve traditional asthma education. The first component is the Motivational Enhancement System for asthma management. It is a mobile 4-session intervention using supported self-regulation and motivational interviewing. Personalized content is based on each participant’s activity level, daily experiences, and goals. The second component is supportive accountability. It is administered by asthma nurses using targeted mobile support (Skype/voice calls) to provide education, promote self-efficacy, and overcome barriers through a motivational interviewing–based framework. The third component is SMS text messaging. It provides reminders for asthma education, medication adherence, and physical activity. The fourth component is physical activity tracking. It uses wearable technology to help meet user-defined physical activity goals. Using a multiphase optimization strategy (MOST) framework, we will test intervention components and combinations of components to identify the most effective mobile intervention. The MOST framework is an innovative, and cost- and time-effective framework that uses engineering principles to produce effective behavioral interventions. We will conduct a component selection experiment using a factorial research design to build an intervention that has been optimized for maximum efficacy, using a clinically significant improvement in asthma. Participants (N=180) will be randomized to 1 of 6 intervention arms. Participants will be recruited from multiple sites of the American Lung Association-Airway Clinical Research Centers network and ambulatory care clinics at the Detroit Medical Center. Data collections will occur at baseline, and 3, 6, and 12 months.

**Results:**

At study completion, we will have an empirically supported optimized mobile asthma management intervention to improve asthma control for AAEAs. We hypothesize that postintervention (3, 6, and 12 months), participants with uncontrolled asthma will show a clinically significant improvement in asthma control. We also hypothesize that improvements in asthma management behaviors (including physical activity), quality of life, symptoms, adherence, and exacerbation (secondary outcomes) will be observed.

**Conclusions:**

AAEAs are disproportionately impacted by asthma, but have been underrepresented in research. Mobile asthma management interventions may help improve asthma control and allow people to live healthier lives. During this project, we will use an innovative strategy to develop an optimized mobile asthma management intervention using the most effective combination of nurse-delivered asthma education, a smartphone app, and text messaging.

**International Registered Report Identifier (IRRID):**

PRR1-10.2196/37946

## Introduction

### Background

Health disparities are evident in many conditions, including cancer, diabetes, and cardiovascular disease. One condition with a significant inequality in health outcomes is asthma. Recent prevalence rates for asthma in the United States show that 7.9% of the adult population has asthma, and this rate is 10.1% among African Americans or Black people. Unfortunately, severity and disease control disparities are significantly worse than the prevalence rates would suggest. For example, the asthma mortality rates are nearly 3 times higher among non-Hispanic African Americans or Black people than among non-Hispanic Whites (22.7 vs 8.1 per million) [1]. Additionally, hospitalization rates are 4 to 5 times higher among African Americans than among Whites [2,3]. Many factors may contribute to these disparities, including both environmental and underlying genetic influences. Urban areas, which often have a predominance of African American residents, are heavily concentrated with risk factors associated with asthma, such as air pollution [4], cockroaches [5], dust mites [6], poor diet [7], poverty [8], stress [9], and violence [10]. Studies have compared African American patients and White patients, and have found that African American patients visit an asthma specialist less often, receive less asthma education, and use an inhaled corticosteroid for persistent asthma less frequently [8,11-13].

### African American Emerging Adults With Asthma

This project will focus on African American emerging adults (AAEAs) between the ages of 18 and 30 years, a developmental period largely neglected in the research literature but known to have some of the worst asthma outcomes along with significant health disparities. While significant research has focused on outcomes in adolescence, most markers of asthma control (mortality, quality of life, and health care utilization) are even worse in emerging adults than in adolescents [14,15]. Part of the reason may be that emerging adulthood represents a period of dramatic change for an individual, with identity exploration and self-focus, increased independence and risk-taking, and decreased parental oversight [16,17]. For the first time, emerging adults are responsible for their own health care, finances, education, and employment. Compounding this problem, many pediatricians stop caring for patients once they turn 18 years. Adult practitioners may not be fully trained or equipped to deal with the unique circumstances of emerging adults transitioning out of adolescence [18] or may rely on the “developmental continuity myth,” that is, the fallacy of applying adult treatments to youth, with little alteration or changes to the interventions [19]. Successful interventions to improve health outcomes must be developed to meet emerging adults’ distinctive developmental needs. 

Literature on interventions to improve asthma management in emerging adults is nearly nonexistent [20-22]. Further, African Americans of all ages are underrepresented in mobile health (mHealth) and eHealth studies [23]. Results of studies with racial/ethnic minority adults suggest that culturally appropriate programs that target specific aspects of asthma management (eg, adherence and physical activity) have largely been successful [24]. Thus, interventions that similarly target AAEAs at the highest risk for poor asthma management and health outcomes may have promise for improving morbidity and mortality rates. Interventions must consider the target group’s distinctive cultural and developmental needs and challenges. This project tests a developmentally and culturally appropriate intervention for AAEAs with persistent asthma.

### Call for Technology-Based Mobile Interventions

There are multiple barriers to intervention delivery, including buy-in at multiple levels (eg, department and community), personnel turnover, and reproducibility. Emerging adults may also be unlikely to complete intensive in-person interventions [25]. Technology-based interventions cannot replicate important human elements of interventions, but they offer advantages in terms of reach, cost, anonymity, and scalability. While there are over 500 asthma-related apps in the Apple Store and Google Play Store, a review in 2019 found that less than 10 have actually been evaluated in clinical trials [26]. Most of these evaluations were conducted with adolescents, were focused on caregivers, or were implemented in school settings. Attrition in eHealth interventions is also common [27], and very few mHealth interventions have been grounded in behavior change theory. The use of SMS text message reminders can improve self-management in people of all ages with asthma [28,29], though the magnitude of improvement tends to be small. Mobile interventions have rarely examined the integration of remote nursing support with a theory-based program. The synergism of such an approach has potential additive effects that urgently require further exploration. Finally, mHealth interventions can be designed to address the concerns and barriers faced by racial/ethnic minority groups or those of low socioeconomic status, as the challenges and goals are often different among such populations [26]. The proposed project will utilize an innovative and cost-efficient framework to identify the most effective combination of intervention components to improve asthma control in AAEAs.

### Theoretical Model

Nearly every guideline notes that asthma education plays a critical role in disease management [30]. Educational strategies based on behavioral theories of change, such as motivational interviewing (MI), are more likely to be effective than strategies that simply provide information. MI is a collaborative goal-oriented style of communication with particular attention to the language of change. It is designed to strengthen intrinsic motivation for and commitment to a goal by eliciting and exploring the person’s own reasons for change within an atmosphere of acceptance and compassion. Research on the mechanisms of effect in MI has concluded that patient “change talk” (ie, statements about their own desire, ability, reasons, or commitment to change) consistently predicts actual behavior change. Several behavior change theories are consistent with MI. First, the Self-Regulation Theory (SRT) has core principles hypothesizing that multiple factors interact to influence behavior. The most influential way in which a person develops expectations and solidifies a behavioral change is through personal experience, which underlies improvement through self-regulation [31]. Zimmerman described self-regulation as a process of the following 3 phases: self-observation, self-judgment, and self-reaction [32], and Zimmerman and Clark adapted these subprocesses for asthma [33]. Through the self-regulatory process, the person is able to observe and learn from experience and determine ways for changing behavior (Figure 1). Second, the Information-Motivation-Behavioral Skills (IMB) model [34] posits that behavior change results from the joint function of the following 3 components: accurate information about risk behaviors (eg, not managing asthma) or their replacement behaviors (eg, benefits of following an asthma management regimen), the motivation to change behavior, and the perceived behavioral skills necessary to perform the behavior (eg, self-efficacy) (Figure 2). A powerful attribute of the IMB model is its ability to improve the self-efficacy needed for behavior change. For the intervention, we have combined the most powerful components of these complementary theories to build an asthma management intervention that not only targets asthma education, but also addresses underlying motivation and provides social support for change.

**Figure 1 figure1:**
[figure not shown]
Self-regulation processes in disease prevention and management.

**Figure 2 figure2:**
[figure not shown]
Information-Motivation-Behavioral Skills model.

### Study Aims

The purpose of this study is to develop an effective mHealth intervention to improve asthma management and asthma control among AAEAs. We have developed and tested technology-based theoretically grounded asthma self-management interventions for AAEAs that will be refined and evaluated as components of a resulting mobile asthma management intervention. These intervention components are based on the SRT or IMB model, and utilize MI. We will evaluate 4 intervention components for synergistic effects. The first component is the Motivational Enhancement System (MES) for asthma management. The MES is a mobile 4-session MI intervention using supported self-regulation to enhance motivation for asthma management and asthma knowledge. Personalized content is chosen by a computer algorithm, and is based on each participant’s self-regulation stage, activity level, daily experiences, and goals. The second component is supportive accountability (SA). SA is administered by asthma nurses using targeted mobile support (Skype/voice calls) to provide education, promote self-efficacy, and overcome barriers through an MI-based framework. The third component is SMS text messaging (TXT). It provides asthma management education. The fourth component is physical activity tracking (PAT). PAT uses wearable technology (eg, a smart watch) for meeting user-defined activity goals as part of the asthma management regimen.

Participants will be recruited from multiple sites of the American Lung Association-Airway Clinical Research Centers network and clinics at Wayne State University/Detroit Medical Center and the University of Michigan. Participants (N=180) with uncontrolled persistent asthma will be randomized to 1 of 6 intervention arms consisting of combinations of the 4 components through a multiphase optimization strategy (MOST) design. The MOST design is an innovative, and cost- and time-effective experimental design that utilizes engineering principles to test behavioral interventions. The MOST design uses an optimization criterion to make decisions and refine the efficacy of each of the intervention components. We will adopt clinically significant improvements in asthma control (defined as a change of ≥3 on the Asthma Control Test [ACT]) as an optimization criterion in a component selection experiment using a randomized factorial design. This experiment is equivalent to conducting multiple pilot randomized clinical trials to evaluate the efficacy of each component, yet uses only a fraction of the sample size, resources, and time. At the completion of this study, we will have developed an empirically supported mobile asthma management intervention to improve asthma control for high-risk AAEAs.

## Methods

### Study Participants and Setting

Phase 2 consists of a clinical trial study. The study will include 180 AAEAs (30 per arm; N=150 + 20% attrition) aged 18-30 years with persistent asthma that is not fully controlled (defined as a score of less than 19 on the ACT) [35]. We have intentionally chosen uncontrolled asthma patients as the program is designed to help take control of their asthma, and these patients would be the most motivated to use such an intervention. Participants must also own or have access to a cellular phone for the duration of the study and have a primary care physician. Recent data from the Pew Research Center demonstrate that 98% of Black individuals currently own a cellular phone, and that 96% of those aged 18-29 years own a smartphone [36]. To encourage participation, we will pay the cellular bill during the 8-week intervention period for all participants, a strategy that we and others have found to be extremely effective in this population. This will be in addition to the participation incentives. The exclusion criteria will be any other significant cardiopulmonary disease (including chronic obstructive pulmonary disease), a greater than 20 pack-year smoking history (as this level has been associated with the development of chronic obstructive pulmonary disease) [37], developmental delay or mental illness such that participation in the program would not be possible, and pregnancy. Women who become pregnant during the course of the study will be allowed to participate with written approval from their physician. Finally, as PAT will be part of the intervention, any subject who is unable to do mild physical activity for any health reason (including asthma) will be excluded. The ability to participate in mild physical activity will be verified by each participant’s primary care provider.

Participants will be recruited through clinical and community locations. Clinical locations will include the American Lung Association-Airway Clinical Research Centers network, as well as clinics at the University of Michigan, Wayne State University, and Detroit Medical Center. Community locations will utilize online recruitment primarily through social media, using procedures we have developed in previous work [38,39]. All components of the trial (including recruitment, signed informed consent, and intervention education components) will be done remotely.

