This study will use a 6-arm incomplete factorial design for the component selection experiment (Table 1). A full factorial design will not be used as some of the experimental combinations cannot be present simultaneously (eg, MES and SA are mHealth and involve human delivery of the same intervention content, and therefore logically cannot be combined), and PAT will be provided to all participants. Byar et al [57] described such incomplete designs, and in particular, we are employing “Design 3,” which is a “2^3^ − Y_AB_ − Y_ABC_” design. This design matches with our experimental combination as MES (A) and SA (B) components cannot occur together. Table 1 shows the incomplete factorial design given the possible combinations of the 4 components [55]. As the full factorial design is not feasible for the current setup, we also considered a 2^3−1^ fractional factorial design with 3 factors but with 4 (2^3−1^) treatment conditions, allowing aliasing of the highest-level interaction (ie, each main effect will be confounded with a 2-factor interaction). However, our design with 6 components is a superset of that 2^3−1^ fractional factorial design and will result in better evaluation of treatment combinations than any fractional factorial (see the study by Byar et al [57]). This design preserves much of the full factorial structure and provides more reasonable results than a fractional factorial design [58]. This design also allows evaluation of the main effect of each component and exploration of interaction effects when components are combined, though more assumptions are needed as a full factorial (=2^3^) is not present. One assumption is a “saturated design” when the combination missing (AB and ABC) is assumed to be 0 or have no effect. The component selection experiment is powered for the main effects and will include 180 participants (or 30 participants per arm).

**Table 1 table1:** Intervention conditions.

Experimental condition	Motivational Enhancement System	SMS text messaging	Supportive accountability	Usual care	Physical activity tracking
1	Yes	No	No	No	Yes
2	No	Yes	No	No	Yes
3	No	No	Yes	No	Yes
4	Yes	Yes	No	No	Yes
5	No	Yes	Yes	No	Yes
6	No	No	No	Yes	Yes

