#### Measurement

Data collection will occur at baseline, 3 months (postintervention), 6 months, and 12 months. At baseline, demographic information, asthma-specific information, and psychosocial information will be collected. The primary outcome will be improvement in asthma control as assessed by the ACT [35,61]. The mediators of asthma control will be based on the evaluation of IMB and SRT constructs, including asthma knowledge, attitudes, motivation, self-management behaviors, and self-efficacy.

Although we have feasibility data for the individual components, we will now obtain data for component combinations. Questionnaires and qualitative methodology will be used to determine recruitment and retention, adherence to the program, suitability and variability of outcome measures used, application and fidelity of the program, and demand/acceptability of the program for patients and professionals [62].

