### Statistical Analysis

We will initially characterize the data heterogeneity and frequency distributions of asthma control, the primary outcome, and all secondary outcomes (asthma management and IMB/SRT constructs). We will check for out-of-range values, outliers, and abnormal values using graphical methods and create descriptive summaries to ensure that all values are within expected ranges. Unexpected findings will prompt checking of raw data for accuracy of data entry and recording. We will analyze the effect of the intervention components on the longitudinal measures of asthma control (ACT) using a mixed effects linear model for repeated measures analysis of variance (ANOVA) of a factorial design. This model will include a fixed effects indicator for each intervention component (SA, MES, TXT, and PAT) and time, along with all interactions with time. Random intercepts will be used to account for the longitudinal nature of the data. Before evaluating which components contribute to a potential change in the ACT score, we will use the model to compare the treatment with all 3 components and the control condition to determine whether the complete intervention is efficacious. If this statistical test is significant, we will identify those components that result in a significant change in the ACT score by examining the interactions between the main effects and time using the strategy advocated by Collins et al [53], which begins with the simplest effects and only adds higher-order interactions if needed. We will use a *P* value of <.05 for the test of total effect (difference between the treatment with all 3 components and the control treatment) and .1 to identify which components contribute to the total effect. We will use a higher threshold for the component selection test because we want to reduce the likelihood of not selecting a component that is contributing to the total effect. Secondary outcomes will be analyzed using a similar approach, but they are not powered. If significant baseline group imbalance is detected for any variable and its correlation with the outcome is 0.30, that variable will be included as a covariate in the inferential analyses. Dropouts and completers will also be compared in terms of baseline variables.

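### The 20% attrition allowance is added to 150 rather than taken from the 180 randomized, so the plan's own attrition rate leaves 144 with complete follow-up, not 150

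*Protocol article*

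**What the plan says.** In Study Participants and Setting the article sets the size of the trial at 180, given as "30 per arm; N=150 + 20% attrition". Study Aims makes clear that the 180 are the people randomized: "Participants (N=180) with uncontrolled persistent asthma will be randomized to 1 of 6 intervention arms". Study Trial Design ties the total to power: "The component selection experiment is powered for the main effects and will include 180 participants (or 30 participants per arm".

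The article gives no effect size, standard deviation or power. It gives the thresholds in Statistical Analysis: .05 for the test of the total effect, "and .1 to identify which components contribute to the total effect". Follow-up runs for a year: "Data collection will occur at baseline, 3 months (postintervention), 6 months, and 12 months".

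**The concern.** The sample-size parenthesis contains a starting number (150), an attrition rate (20%) and, with the words before it, a total (180). A reader will take 150 as the number that should remain after dropout and 180 as the number to be randomized so that it does. An attrition rate is a share of those who enter. Applied to 180 it does not give 150 back.

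At stake is whether the trial reaches its own target at the attrition it plans for. The cushion is not idle, because the Limitations section names both differential loss to follow-up and keeping participants for 12 months as difficulties.

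**Working it through.** **Inputs.** 180 randomized to 6 arms, 30 per arm (Study Aims; Study Participants and Setting). 150 before the allowance, which is 150/6 = 25 per arm. Attrition d = 0.20 (Study Participants and Setting).

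**Reproducing the plan's figure.** Adding the allowance, n × (1 + d):
- total: 150 × 1.20 = 180
- per arm: 25 × 1.20 = 30

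This matches the article exactly.

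**The usual inflation.** Dividing by the retained share, n / (1 − d):
- total: 150 / 0.80 = 187.5, so 188
- with equal arms: 25 / 0.80 = 31.25, so 32 per arm and 6 × 32 = 192

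This does not give 180. The stated total is 188 − 180 = 8 short, or 192 − 180 = 12 short with equal arms.

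**What 180 delivers at 20% attrition.**
- total: 180 × 0.80 = 144
- per arm: 30 × 0.80 = 24
- shortfall against 150: 6 in total, 1 per arm

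**The attrition that 180 can absorb.** (180 − 150) / 180 = 30/180 = 16.7%.

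**Effect on precision.** With equal allocation, the standard error of any fixed contrast scales with 1/√n. √(150/144) = 1.021, so it is about 2% larger.

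**Effect on power (illustration).** The article states no power, so 80% and 90% at n = 150 are assumed, with two-sided tests (sidedness is also not stated). Power at 144 is Φ[(z₁₋α/₂ + z_power) × √(144/150) − z₁₋α/₂]:

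| α (two-sided) | Assumed power at 150 | Power at 144 |
|---|---|---|
| .05 | 80% | 78.4% |
| .05 | 90% | 88.8% |
| .10 | 80% | 78.6% |
| .10 | 90% | 88.9% |

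The loss is between 1.1 and 1.6 percentage points.

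**The case against.** Four things can be said for the plan.

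1. *The 150 may not be the power target.* No power calculation is shown, and Study Trial Design says the experiment "is powered for the main effects and will include 180 participants (or 30 participants per arm", which attaches the power statement to 180. This stands as a limit: that the power rests on 150 is inferred from how the parenthesis is built. It does not rescue the arithmetic, since 150, 20% and 180 still disagree on any reading in which 20% is the share lost, and the article gives the 20% no other meaning.

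2. *144 is a count of completers.* Statistical Analysis plans a mixed model with random intercepts on the repeated asthma-control scores and states no restriction to completers. Someone lost after 3 or 6 months would still contribute. This also stands: 144 is nearer a floor on the information than the number analysed. The timing of the losses is not given, so the softening cannot be quantified.

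3. *The effect is slight.* It is, and this decides the weight of the point.

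4. *Detail may sit in a fuller document.* That is true of the power calculation. It does not apply here, because no fuller document can make a 20% loss from 180 leave 150.

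A reader might go further. Table 1 shows that the Motivational Enhancement System (MES) and supportive accountability (SA) are each compared with the same two arms that have neither, so each of those effects uses four of the six arms. It is tempting to infer that the power statement overlooked this. The document does not support that. It gives no power, effect size or contrast size, so nothing shows that the calculation assumed all participants in every contrast. The article itself notes that the two components cannot occur together and that the incomplete factorial needs more assumptions. The contrast sizes may well be set out in the full protocol or analysis plan.

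**Conclusion.** The point holds as a minor arithmetic error. The allowance was made by adding 20% to 150; at 20% attrition the 180 randomized leave 144 with complete follow-up (24 per arm), and 150 is kept only if attrition stays at or below 16.7%. These figures follow from the article's own numbers and need no assumption beyond reading attrition as a share of those randomized.

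The consequence for power rests on more: that 150 was the evaluable target, that planned power was 80% to 90%, that tests are two-sided, and that dropouts contribute nothing. Even so, the loss is only 1 to 2 percentage points. The finding says nothing against the choice of 180 itself, and it is not evidence that the trial is underpowered for any component.

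**What to change.** Keep 180 and correct the sentence in Study Participants and Setting in one of two ways:
- *180 randomized (30 per arm); with 20% attrition, 144 with complete follow-up (24 per arm)*; or
- *180 randomized (30 per arm), which allows for 16.7% attrition and retains 150 (25 per arm)*.

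If 20% remains the expected attrition, any power statement for the main effects, here or in the fuller documents, should be based on 144.

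The cost is one corrected sentence and a slightly less favourable stated figure. No extra participants are needed, and randomization and analysis do not change. Randomizing 188 (192 for equal arms) would also restore 150, but the size of the shortfall hardly calls for it.
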